### cRCT Component

#### Site Selection and Randomization

The study clusters comprise 22 of the 30 administrative wards in the county. The 30 wards were categorized into 5 strata based on community type (ie, periurban, rural fishing, or rural nonfishing) and whether the proportion of girls on PrEP is above or below the median, using MoH programmatic data. (Although the geography and PrEP use criteria define 6 strata, only 1 ward in the county fell within the urban, low PrEP use stratum. Because it was not possible to create a pair of intervention and control wards in this stratum, it was excluded.) The 22 study wards were purposively selected to ensure an even number of wards within each stratum and a balanced distribution of wards across strata. Randomization was completed by RTI statisticians once the 22 study wards are selected and placed into strata. Within each stratum, wards were randomly allocated to the intervention or control arms in a 1:1 ratio. After randomization, we created pairs of intervention and control wards within each stratum and determined the order in which they would be enrolled in the study based on the location of each ward, to minimize the risk of contamination while ensuring the feasibility of implementation. Subsequently, one intervention and control site pair were randomly selected from each stratum for inclusion in the qualitative component. Allocation was revealed to the investigators before community mapping (see the Recruitment and Screening section) and to the participants after their enrollment into the study.

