#### Eligibility Criteria

To be eligible, potential participants must be females aged 15 to 24, currently in a sexual relationship with a male partner for at least 1 month, and vulnerable to HIV per a modified version of the DREAMS eligibility screening tool. To reflect the population most likely to participate in this intervention in a programmatic setting, they must be either taking PrEP or interested in taking PrEP (ie, she thinks that she would benefit from PrEP but is not currently taking it). In addition, they must be residents of the applicable study ward; willing and able to attend support clubs; willing and able to provide adequate contact information; fluent in English, Dholuo, or Kiswahili; and able and willing to provide informed consent (or assent and parental consent for nonmature minor participants aged 15 to 17). Potential participants are excluded if they are living with HIV (by self-report); planning any long-term travel or relocation in the next 12 months; or have any condition that the site PI or designee determines would preclude participation.

Individuals who do not meet the criteria for participation in this trial (ie, screen failure) because of criteria that are likely to change over time may be rescreened. Examples include not being resident of the ward or not being interested in taking PrEP.

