#### Recruitment and Screening

Recruitment occurs simultaneously in each pair of wards before moving on to the next pair and focuses on the catchment areas of 2 to 4 health facilities in each ward. Before recruitment, community mapping is conducted to identify key stakeholders, referral resources, locations where adolescent girls and young women gather, and locations where men gather. Recruitment takes place at venues identified through community mapping, including health facilities, schools, churches, DREAMS Safe Spaces, youth groups, and community markets. To ensure that the study findings are generalizable to adolescent girls and young women across the 15- to 24-year age range, we aim to enroll at least 25% of the study participants from the 15- to 19-year age group who have lower rates of PrEP use but have similar HIV incidence to the 20- to 24-year age group [47,48]. Attendees interested in the study are invited to meet with the research assistant after the recruitment meeting to discuss questions, obtain additional information, and schedule an appointment for informed consent, eligibility screening, and, if eligible, for enrollment.

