##### Intervention Delivery

Before delivery, the intervention manual and training tools were updated to reflect lessons learned during the pilot and the change to implementation outside of DREAMS. Because age restrictions on PrEP in DREAMS did not permit us to pilot the intervention with adolescent girls aged 15 to 17 years, we pretested the activities with 12 to 15 adolescent girls in this age range over a 1-month period to obtain feedback on comprehension and relevance of the content and how best to support participation.

Delivery takes place in 4 phases, with activities occurring concurrently in 2 wards during phase 1 and in 3 wards during phases 2 to 4. In each ward, the intervention is conducted over a 6-month period with intervention implementation beginning about 1 week after enrollment concludes. Each new phase of the intervention commences immediately after the activities in the previous phase are concluded. This phased approach minimizes staff burden and allows for close monitoring of implementation to identify and correct problems early on.

The intervention activities include sensitization of MoH clinics, intervention staffing and training, community sensitization sessions, Buddy Days, support clubs, and monitoring and quality assurance.

For sensitization of MoH clinics, before study initiation in each intervention ward, we collaborate with the facility in-charges from each of the 2 to 4 health facilities selected for study recruitment to identify PrEP delivery staff and schedule a half to one day training to introduce the study and discuss relationship-related challenges to PrEP use, with the goal of ensuring that the counseling support offered at the clinics complements the messages provided through the intervention. We also review PrEP adherence and couples’ counseling and disclosure approaches to more comprehensively address adherence challenges commonly experienced by adolescent girls and young women.

Intervention staffing and training within each ward is delivered by a set of 2 to 4 mentors (ie, women slightly older than the participants who have completed at least some secondary education and are rooted in their communities), an experienced male community organizer, and clinicians and counselors with experience in PrEP provision to adolescent girls and young women (hereafter “intervention providers”). Staff supervisors train each cadre over 1 to 3 days to review the intervention manual and to practice the required activities.

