#### Data Collection

Data collection visits occur simultaneously in each pair of wards at enrollment, and months 3, 6, and 12 (Table 3). At enrollment, interviewer-administered questionnaires are used to assess sociodemographics, relationship characteristics, IPV, behavioral HIV risk factors, and history of PrEP use. Measures are repeated in follow-up questionnaires to document changes in relevant characteristics, attitudes, and behaviors.

DBS samples are collected via fingerprick at months 6 and 12 from all participants who report initiation or continuation of PrEP since the last visit. For participants who report discontinuation of PrEP, reasons for discontinuation are recorded, but DBSs are not collected. Due to storage and transport challenges, DBS samples are also not collected for participants who have relocated outside the county and have follow-up visits conducted by phone or at a remote location. DBS samples are stored in freezers at the IRDO laboratory and then shipped to the laboratory at the University of North Carolina Center for AIDS Research Clinical Pharmacology and Analytical Chemistry Core for quantification of drug concentrations by liquid chromatography-tandem mass spectrometry technology [60].

**Table 3 table3:** Participant timeline.

Procedures			Month 0 (BL^a^)		Month 1		Month 2		Month 3 (3 MFU^b^)		Month 4		Month 5		Month 6 (6 MFU)		Month 7		Month 8		Month 9		Month 10		Month 11		Month 12 (12 MFU)
Assess and confirm eligibility			✓																								
Informed consent			✓																								
Enrollment			✓																								
Locator information and update			✓						✓						✓						✓						✓

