**Primary outcomes**		
	Effective PrEP^a^ use (biomarker assessment)	Percentage of all study participants with biomarker TFVdp^b^ levels indicating consistent PrEP use (≥4 doses per week) for the past 2 months. [68,69]. Represents a composite outcome of PrEP initiation and high execution to capture these key steps in the HIV prevention continuum. Collected at months 6 and 12 only.

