#### Analysis Approach

Descriptive and bivariate statistics will be used to compare participant characteristics in the intervention and control arms and those who completed the study versus those lost to follow-up. Outcomes will be modeled using an intent-to-treat approach with mixed effect logistic and linear regression models. Model predictors will include treatment assignments, randomization strata, and a random effect for ward (cluster) within stratum that is assumed to be independent and normally distributed with mean 0. If the cluster randomization does not adequately balance baseline characteristics across arms, we will conduct exploratory analyses controlling for those characteristics. We will analyze the data from each of the 2 time points separately and the primary outcomes analyses will use a type I error rate of 0.025 at each time point.

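### The primary model omits individual baseline PrEP use, although investigators knew ward allocation before recruitment; adjustment is only exploratory and depends on an undefined judgment of imbalance

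*Protocol article*

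**What the plan says.** **Order of events.** Under Site Selection and Randomization, the 22 wards were allocated first. "Allocation was revealed to the investigators before community mapping"; participants are told their arm only after they enroll. Under Recruitment and Screening, mapping comes before recruitment and supplies its sites: "Recruitment takes place at venues identified through community mapping, including health facilities, schools, churches, DREAMS Safe Spaces, youth groups, and community markets". Both wards of a pair recruit at the same time. The article does not say whether the recruiting research assistants know the arm.

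**Who can enroll.** Under Eligibility Criteria, "they must be either taking PrEP or interested in taking PrEP". No quota by PrEP status is given; the only composition target is a minimum share aged 15 to 19.

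**Strata.** Wards are classified by community type and by whether the ward's proportion of girls on PrEP lies above or below the median in Ministry of Health data. This is a ward-level split, not the status of the women enrolled.

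**Baseline measurement.** At enrollment, "interviewer-administered questionnaires are used to assess sociodemographics, relationship characteristics, IPV, behavioral HIV risk factors, and history of PrEP use". Dried blood spots are taken only at months 6 and 12, so baseline use is self-reported.

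**Outcome and model.** Table 4 defines the primary outcome as "Percentage of all study participants with biomarker TFVdp" levels showing consistent use, which includes women already on PrEP at entry. Under Analysis Approach, the predictors are arm, strata and a random ward effect. Adjustment for other characteristics is conditional and exploratory: "If the cluster randomization does not adequately balance baseline characteristics across arms, we will conduct exploratory analyses controlling for those characteristics". By contrast, the process-evaluation models for mechanisms of change control for the baseline value unconditionally.

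**The concern.** Randomizing wards balances wards in expectation. It does not by itself balance the women recruited afterwards by a team whose investigators know the arm. If venue choice, or the choice of whom to approach, leads to relatively more current users in one arm, the outcome difference carries that mix with it. Stratifying on a ward-level median split does not prevent this.

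The plan's response has two weaknesses. If an imbalance is seen, the primary result stays uncorrected and only an exploratory analysis addresses it. And because neither the trigger nor the variables are fixed, the choice of adjusted model can follow the data. At stake are a false difference in either direction and some precision lost to variation in user mix between wards.

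**Working it through.** **Yardstick.** Sample Size Considerations gives a 15-point difference, 11 wards per arm, 60 analysed per ward, type I error 0.025 per time point, ward SD up to 10 points, control use below 50% and power of at least 80%. A simulation of that logistic model used normal ward effects, a Wald test, 4000 runs, no strata, and SD converted to the logit scale as 0.10/[p(1−p)], which is an assumption. Two-sided power was 0.83 at 49% control use, 0.80 at 40%, 0.77 at 30% and 0.73 at 20%; one-sided it was 0.89, 0.87, 0.84 and 0.81. The stated figure is reproduced near the 50% boundary two-sided, and at all four rates one-sided. Sidedness is not stated. The 15-point difference serves as the yardstick below.

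**Size of the false difference.** With no true effect and the same rates in both arms:

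false difference = (difference between arms in share of baseline users) × (effective use in users − effective use in non-users)

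The documents give neither term by arm or by baseline status. The Introduction reports TFVdp levels suggesting high adherence in 4% to 8% of PrEP users at about 6 months after initiation. All other rates below are assumptions. Results are in percentage points.

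| Effective use, users / non-users | 5-point imbalance | 10-point | 20-point |
|---|---|---|---|
| 4% / 5% | −0.05 | −0.1 | −0.2 |
| 8% / 5% | 0.15 | 0.3 | 0.6 |
| 4% / 0% | 0.2 | 0.4 | 0.8 |
| 8% / 0% | 0.4 | 0.8 | 1.6 |
| 20% / 5% | 0.75 | 1.5 | 3.0 |
| 40% / 5% | 1.75 | 3.5 | 7.0 |

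At a 10-point imbalance, 0.8/15 = 5% of the design difference, 1.5/15 = 10% and 3.5/15 = 23%.

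**Effect on the test, normal approximation.** SE² = (1/11) × the sum over arms of [SD² + p(1−p)/60], with a two-sided critical value of 2.24 and, as an assumption, 30% v 40% baseline users. For 20% / 5% effective use, p = 0.3×0.20 + 0.7×0.05 = 0.095 in control and 0.4×0.20 + 0.6×0.05 = 0.11 in intervention. With a ward SD of 3 points, SE = 0.021 and 0.015/0.021 = 0.71, so the rejection rate is 0.065. With an SD of 10 points it is 0.033. For 40% / 5% the rates are 0.21 and 0.068. The nominal rate is 0.025.

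**Effect of the covariate, simulation.** Assumptions: effective use 40% in users and 10% in non-users, control arm 30% users, 60 per ward, 5000 runs, no true effect, two-sided 0.025. The predicted false difference is 10 × 0.30 = 3 points or 20 × 0.30 = 6 points.

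| Ward SD (logit) | Users, control v intervention | Rejection, planned model | Rejection, with baseline use |
|---|---|---|---|
| 0.25 | 30% v 30% | 0.033 | 0.035 |
| 0.25 | 30% v 40% | 0.148 | 0.036 |
| 0.25 | 30% v 50% | 0.487 | 0.040 |
| 0.5 | 30% v 30% | 0.044 | 0.046 |
| 0.5 | 30% v 40% | 0.104 | 0.044 |
| 0.5 | 30% v 50% | 0.289 | 0.040 |

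Rates above 0.025 under balance reflect Wald tests with 22 clusters and affect both models alike.

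**Precision.** With balanced arms and a conditional log odds ratio of 0.6, power goes from 0.847 to 0.882 (SD 0.25) and from 0.547 to 0.566 (SD 0.5) when baseline use is added. The gain is small.

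**The case against.** The case against rests on these points.

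- **Concealment is better than the order of events suggests.** Participants do not know their arm at enrollment, and paired wards recruit at the same time under the same criteria and venue types. Women cannot self-select on what the study tells them. This stands: what remains is staff choice of venue and of whom to approach, which is possible but not shown.
- **The protocol's nearest figure makes the bias small.** At 4% to 8% effective use in users, a 10-point imbalance gives under 1 point. With 3-month persistence of 5% to 37% in the Introduction, baseline use may also predict later use poorly. This stands as well. The larger figures depend on assumed rates, and the documents do not support calling baseline use the strongest predictor.
- **The plan is not silent.** It compares baseline characteristics by arm, offers adjusted analyses, acknowledges the risk under Limitations, and adds covariates related to missingness if missing data exceed 10%. None of this commits the primary model to baseline PrEP use. An unseen analysis plan may name covariates, but this article lists the primary predictors and labels further adjustment exploratory, which is a stated choice.

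Two stronger readings are tempting. A reader might infer that rescreening shifts the mix by arm, since of the criteria that may change the protocol says: "Examples include not being resident of the ward or not being interested in taking PrEP". But that rule applies equally in all wards. A reader might also point to clinic training, because "before study initiation in each intervention ward, we collaborate with the facility in-charges". It is the one arm-specific activity placed before enrollment, but nothing in the text shows that it changed who was recruited.

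**Conclusion.** The point holds as a weakness in the prespecified primary analysis. A variable that the plan collects, and that the outcome definition makes relevant, is left out of the primary model, and adjustment depends on an undefined judgment. A reader might go further and infer that the primary comparison is biased, or that recruiters or participants knew the arm. The documents do not support either: they report no baseline mix by arm, they do not say what recruiters knew, and participants learn their arm only after enrollment.

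For a 10-point imbalance the false difference is under 1 point at the Introduction's rates and 1.5 to 3.5 points at the assumed higher rates, against a design difference of 15. The inflated rejection rates apply only under the assumed gaps. The precision gain is minor. The change is worth making because it costs almost nothing and removes a data-dependent choice.

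**What to change.** State in the analysis plan, before outcomes are compared by arm:

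- The primary model at each time point includes arm, strata, the random ward effect and self-reported PrEP use at enrollment (yes/no), whatever the observed balance.
- The effect is reported as a standardized risk difference, the absolute scale on which the trial was powered, alongside the odds ratio.
- The model without baseline use is a sensitivity analysis, and baseline PrEP use is tabulated by arm.

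**Cost.** The change needs wording only. The enrollment questionnaire covers PrEP history, and the exploratory uptake outcome already needs to know who was not on PrEP at baseline.

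**Downsides.** The odds ratio becomes conditional on the covariate, which the standardized risk difference addresses. Self-report corrects only for what it measures, not for motivation or other unmeasured differences. If the early clinic training had itself raised use before enrollment, adjustment would remove that part of the effect; the sensitivity analysis keeps this visible.

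Two further changes are not recommended. No case has been made for adding age group. Moving the clinic training would alter delivery mid-trial, with enrollment already complete in 16 of 22 wards by December 2024.

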### Sample Size Considerations

The study is powered to identify an absolute difference of 15% between intervention and control arms for the primary outcomes: the proportion with effective PrEP use at month 6 and month 12. Power calculations are conducted using simulations based on the logistic model with normally distributed ward (cluster) effects and assuming 11 wards per treatment arm with type 1 error of 0.025 to account for separate analyses at each of 2 time points. With 60 participants per ward, we will have ≥80% power to detect a 15% difference in the outcome as long as the SD for ward variation is ≤10% and the level of effective PrEP use in control wards remains <50% (far higher than observed in recent trials and demonstration projects). To allow for up to 20% loss to follow-up, our total sample size will be 1584 participants: 72 adolescent girls and young women in each of the 22 wards (11 wards per arm).

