### Data Analysis: Clinical Trial

#### Outcomes and Hypotheses

The primary outcomes of the study will be the proportion of study participants with effective PrEP use, defined in Table 4, evaluated immediately postintervention, at month 6, and at month 12 to gauge the persistence of intervention effect. TFVdp levels will be dichotomized by Clinical Pharmacology and Analytical Chemistry Core laboratory specialists to delineate between consistent (≥4 doses per week) versus inconsistent (<4 doses per week) adherence [68]. The aim 1 hypothesis is that the proportion of participants with effective PrEP use at (a) month 6 and (b) month 12 will be *higher* in the intervention versus control arm.

**Table 4 table4:** An overview of key measures for the cluster randomized controlled trial, collected at enrollment and months 3, 6, and 12, unless otherwise noted.

Measure		Method

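### Efficiency, not error: Holm's procedure across month 6 and month 12 would give more power than a fixed 0.025 at each, under the same family-wise bound of 0.05

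*Protocol article*

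**What the plan says.** Effective PrEP use is assessed as the primary outcome at two times. Month 6 falls at the end of the intervention, and the article (Outcomes and Hypotheses) adds an assessment "at month 12 to gauge the persistence of intervention effect". The aim 1 hypothesis is directional and covers both: "the proportion of participants with effective PrEP use at (a) month 6 and (b) month 12 will be" higher in the intervention arm.

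The error rate is fixed in two places that agree. Sample Size Considerations uses "type 1 error of 0.025 to account for separate analyses at each of 2 time points". Analysis Approach reads: "We will analyze the data from each of the 2 time points separately and the primary outcomes analyses will use a type I error rate". It sets that rate to 0.025 for month 6 and again for month 12. Neither place lets the level at one time point depend on the result at the other.

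On power, the article says: "With 60 participants per ward, we will have ≥80% power to detect a 15% difference in the outcome". This is conditional on a between-ward SD of at most 10% and a control rate below 50%. It is a figure per time point. The article gives no probability of succeeding at both, no correlation between the two test statistics, and no sidedness.

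**The concern.** With two primary hypotheses, a fixed 0.025 for each leaves some of the permitted error unused once one hypothesis is rejected. Only one hypothesis can then still be falsely rejected, and it could be tested at 0.05 without breaking the overall bound.

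As an illustration, take p = 0.001 at month 6 and p = 0.03 at month 12. Under the stated rule month 12 is not significant. Under Holm's procedure both are, at the same family-wise level.

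Month 12 comes six months after the intervention ends, so a smaller effect there is plausible, and that is where the fixed split costs most. The 22 wards are already randomized, so power cannot readily be bought with more clusters.

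**Working it through.** **1. The plan's own figures.**
- Error: 0.025 + 0.025 = 0.05. If the two tests were independent it would be 1 − 0.975² = 0.0494. The article does not write 0.05; it is inferred from 2 × 0.025.
- Power: a logistic-normal simulation used 11 wards per arm, 60 per ward, a 15-point difference, a two-sided 0.025 Wald test, and a ward SD of about 0.42 on the logit scale (10 points at a rate of 50%). It gives 99%, 92%, 83%, 79% and 81% at control rates of 10%, 20%, 30%, 40% and 50%. The stated floor of 80% is reproduced to within about a point. The logit scale for the SD and the two-sided test are assumptions.

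**2. Error control under Holm.** Let p(1) ≤ p(2). Reject the hypothesis with p(1) if p(1) ≤ 0.025; if so, reject the other if p(2) ≤ 0.05.
- Both nulls true: any false rejection requires p(1) ≤ 0.025. This is the same event as under the split, so the probability is at most 0.05.
- One null true: a false rejection requires that null's p ≤ 0.05, so the probability is at most 0.05.
- Neither step uses the correlation. In simulation (2,000,000 runs) the error with one true null was at most 0.045, and no rejection made by the split was lost.

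**3. Power when each time point has 80%.** The test statistic has mean δ = z(0.9875) + z(0.80) = 2.241 + 0.842 = 3.083. The chance of passing 0.05 is then Φ(3.083 − 1.960) = 0.869. With correlation 0 this can be done by hand:
- Both, split: 0.80² = 0.640.
- Both, Holm: 0.640 + 2 × 0.80 × (0.869 − 0.800) = 0.751.
- One given time point, Holm: 0.800 + 0.80 × (0.869 − 0.800) = 0.855.

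For other correlations, from the bivariate normal distribution:

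| Correlation | One time point, split → Holm | Both, split → Holm | At least one, either rule |
|---|---|---|---|
| 0 | 80.0% → 85.5% | 64.0% → 75.1% | 96.0% |
| 0.5 | 80.0% → 84.6% | 68.7% → 77.8% | 91.3% |
| 0.9 | 80.0% → 83.2% | 74.9% → 81.4% | 85.0% |

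**4. Power above the floor.** At 92% per time point (a 20% control rate in step 1), the chance of both rises from 84.6% to 90.9% at correlation 0 and from 89.4% to 92.9% at 0.9, a gain of about 4 to 6 points. At 99% (a 10% control rate), it rises from 98.0% to 99.1% and from 98.5% to 99.2%, about 1 point.

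**5. An effect that wanes.** With an assumed 80% power at month 6 and 40% at month 12, month 12 power rises from 40% to about 49% to 51% over the same correlations. If the standardized effect at month 12 is half that at month 6, it rises from 24% to about 32% to 34%.

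**The case against.** The strongest reply is that nothing here is wrong. The split is prespecified, controls error and agrees with the sample-size section. It lets each time point stand alone, with a matching 97.5% interval and no dependence on the other result. All of that stands, so this is an improvement and not a correction.

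The gain also depends on power being near the floor. The article regards control rates near 50% as far above what recent studies have seen. At a 10% control rate with the full 15-point effect, Holm adds about 1 point for both. That stands too, although the planned effect may not be reached at month 12.

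Three stronger readings are tempting, and the article supports none of them.
- A reader might infer that p = 0.03 at month 12 would be declared a failure of persistence. The article says only that month 12 gauges persistence; it gives no rule that turns a non-significant result into failure.
- A reader might infer that success requires both time points. No such criterion is stated, and the chance of at least one significant result is the same under either rule.
- A reader might infer that the trial is underpowered or needs more participants. The stated power at 0.025 is reproduced and stays valid.

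Finally, the change would come mid-trial with open allocation. Investigators knew the assignment before community mapping, participants learn it after enrollment, and 16 of 22 wards had completed enrollment by December 2024. This bears on how the amendment is made, not on the statistical comparison.

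**Conclusion.** The point holds as a cheap gain in efficiency. The fixed 0.025 is valid, but no correlation, effect size or sidedness makes it better than Holm for the two tests. At the stated floor of 80% power, Holm adds about 3 to 5.5 points at each time point and 6.5 to 11 points for significance at both. The gain falls as power rises and is larger at month 12 if the effect wanes.

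The direction rests on no assumption beyond the family-wise level of 0.05 implied by the article. The sizes rest on normal test statistics, two-sided tests and an assumed correlation of 0 to 0.9.

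**What to change.** In Analysis Approach, replace the fixed level at each time point with a sentence to this effect: the two primary comparisons, at month 6 and month 12, will be tested by Holm's procedure at a family-wise error rate of 0.05, with the same sidedness at both steps. State that sidedness. Leave the sample-size calculation at 0.025 as a conservative figure.

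The cost is one sentence, with no change to sample size or conduct. Because allocation is open and the trial is under way, the change should be a documented amendment with the prior ethics committee approval that the article requires, dated before any comparison of outcomes by arm. By the article's timeline there is room: data collection is expected to end in May 2026, with results by mid-2027.

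There are two smaller costs. The second decision needs both p values, so month 6 cannot always be closed before month 12 is known. And if 97.5% intervals are reported (the article specifies none), one may include no effect although Holm rejects at the second step. The amendment should say how such a case will be presented.
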